### **b. Child selection**

During data collection, team members will generate a line list of children in the household aged 6 months–6 years and 7 years–14 years, ordered youngest to oldest. The team will select one child randomly (using simple random sampling) from each age group using a random number generator. Children will be assigned a unique study ID. The caregiver of the selected child(ren) will be consented, enrolled, and interviewed (if consent obtained) using the vaccination coverage assessment questionnaire. DBS samples will also be collected on selected children aged 1y–14y.

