### **c. Sample size:**

Logistics and available resources determined that the maximum number of households that can be visited by the field teams is 625 households in both Kutupalong and Nayapara camps. To estimate the expected number of children enrolled we made the following assumptions (Table 1):

- 65% of households will have at least one child aged 6m–6y (for DBS calculations, 60% will have a child aged 1y–6y) and 65% of households will have at least one child aged 7y–14y
- Household non-response rate (i.e., no one home) is 20%
- Child non-response rate (e.g., refusal, child absent from home) is 1% for all children for the survey component of the assessment (primary respondent for the questionnaire is the mother or caregiver); for DBS specimen collection, non-response is estimated at 10% for children 1y–6y and 30% for children aged 7y–14y
- Coverage for 3 pentavalent doses and the proportion of children with protective antibody levels for tetanus is 50%

Given these assumptions, the expected number of children enrolled for the survey is 322 children aged 6m–6y and 322 children aged 7y–14y in each of the camps (Table 1). This results in a 95% Wilson-Score confidence with precision of 5.6% in each age group. The expected number of enrolled children for DBS is 270 children aged 1y–6y and 228 children aged 7y–14y in both the Kutapalong and Nayapara camps (Table 1); precision is 6.1% and 6.7% in each age group, respectively.

The expected total number of children enrolled in both Kutupalong and Nayapara camps is 1,288 for the survey; among these children, 996 will be enrolled for DBS specimen collection.

Table 1. Kutupalong and Nayapara sample size calculations

| Component       | Age group | # Households Visited | Proportion of households with an eligible child | Household Non-response (i.e., no one home) | Child Non-response (i.e., refusal, not home) | # children expected to be enrolled | Coverage/ seroprevalence | Precision |
|-----------------|-----------|----------------------|-------------------------------------------------|--------------------------------------------|----------------------------------------------|------------------------------------|--------------------------|-----------|

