**d. Sample size for makeshift camps:**

Thirteen (13) households in 56 clusters will result in a total of 728 households visited. To estimate the expected number of children enrolled we made the following assumptions (Table 1):

- 65% of households will have at least one child aged 6m–6y (for DBS calculations, 60% will have a child aged 1y–6y) and 60% of households will have at least one child aged 7y–14y
- Household non-response rate (i.e., no one home) is 5%
- Child non-response rate (e.g., refusal, child absent from home) is 1% for all children for the survey component of the assessment (primary respondent for the questionnaire is the mother or caregiver); for DBS specimen collection, non-

response is estimated at 10% for children 1y–6y and 20% for children aged 7y–14y

- Coverage for 3 pentavalent doses and the proportion of children with protective antibody levels for tetanus is 50%

Given these assumptions, the expected number of children enrolled for the survey is 445 children aged 6m–6y and 411 children aged 7y–14y in the settlements (Table 1). With a design effect of 1.7 (6m–6y) and 1.6 (7y–14y), this results in a 95% Wilson-Score confidence with precision of 6.2% in both age groups. The enrolment for DBS is 374 children aged 1y–6y and 332 children aged 7y–14y in the settlements (Table 1); the design effect is 1.6 and 1.5, respectively, resulting in a precision of 6.5% (1y–6y) and 6.7% (7y–14y).

The expected total number of children enrolled in the makeshift settlements is 856 for the survey; among these children, 706 will be enrolled for DBS specimen collection.

Table 3. Makeshift camp sample sizes:

| Component       | Age group | # Clusters | # Housholds per cluster | Proportion of households with an eligible child | Household Non-response (i.e., no one home) | Child Non-response (i.e., refusal, not home) | # children expected to be enrolled | Design effect** | Precision |
|-----------------|-----------|------------|-------------------------|-------------------------------------------------|--------------------------------------------|----------------------------------------------|------------------------------------|-----------------|-----------|
| Coverage survey | 6m–6y     | 56         | 13                      | 65%                                             | 5%                                         | 1%                                           | 445.0                              | 1.7             | 6.2%      |

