## **Data Collection, Management and Analysis Plan**

Data collection will take place in Kutupalong refugee camp over the course of about 1 week, in makeshift and informal settlements over the course of 3–4 weeks, and Nayapara refugee camp over the course of about 1 week.

Data will be collected on tablets (Lenovo). Data will be uploaded daily to a Kobo server to enable remote monitoring of data quality. All teams will carry hard copies of the questionnaires as back-ups in case the tablet fails at any point.

A daily random check of entered data will be conducted by the survey manager. Team leaders with respective program personnel will ensure quality data collection at field level.

Vaccination coverage, seroprevalence and respective 95% confidence intervals will be estimated for 6m–6yr old children and 7–14yr old children using survey methods that account for the cluster design and sampling weights.

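### Registered-camp precision is that of an equal-probability sample of children and leaves out the weighting loss from drawing one child per household

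*Protocol*

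**What the plan says.** In the registered camps, households are drawn by simple random sampling from the refugee lists. Within a household (Protocol, section 5, I b, Child selection): "The team will select one child randomly (using simple random sampling) from each age group using a random number generator". The settlements use the same draw as their third stage.

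The camp sample size (section 5, I c) starts from a logistic ceiling: "the maximum number of households that can be visited by the field teams is 625 households". It assumes that "65% of households will have at least one child aged 6m–6y" (the same share for 7y–14y; "for DBS calculations, 60% will have a child aged 1y–6y"), and "Household non-response rate (i.e., no one home) is 20"%. Child non-response is 1% for the survey and 10% or 30% for DBS, and the proportion to be estimated is 50%. For the survey it concludes: "This results in a 95% Wilson-Score confidence with precision of 5.6% in each age group". Table 1 gives 6.1% and 6.7% for DBS. It has no design-effect column.

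The settlement calculation (section 5, II d) does have one: "With a design effect of 1.7 (6m–6y) and 1.6 (7y–14y), this results in a 95% Wilson-Score confidence with precision of 6.2"%. The DBS rows there use 1.6 and 1.5.

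The Data Collection, Management and Analysis Plan says that estimates will be made "using survey methods that account for the cluster design and sampling weights".

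**The concern.** Households, not children, have equal selection probabilities in the camps. A child who is alone in the age group is taken with certainty once the household is sampled. One of three eligible children is taken with probability 1/3. The design weight is therefore proportional to the number of eligible children in the household. Unequal weights widen the interval unless they are unrelated to sampling, which is not the case here.

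The analysis section accepts this by committing to weights, but the camp precision is worked out as though there were none. Precision is the protocol's only statement of what a sample fixed by logistics will deliver for the primary coverage and seroprevalence objectives, so a reader would plan on intervals narrower than the design gives.

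**Working it through.** **1. Expected numbers per camp** (inputs from section 5, I c and Table 1): households × share with an eligible child × (1 − household non-response) × (1 − child non-response).

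- Survey, either age group: 625 × 0.65 × 0.80 × 0.99 = 321.75
- DBS 1y–6y: 625 × 0.60 × 0.80 × 0.90 = 270.0
- DBS 7y–14y: 625 × 0.65 × 0.80 × 0.70 = 227.5

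All agree with Table 1.

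**2. Stated precision.** The 95% Wilson interval with continuity correction at p = 0.5 has half-width [1 + z√(z² − 1/n + n)] / [2(n + z²)], with z = 1.96.

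| n | Wald | Wilson | Wilson, continuity-corrected | Stated |
|---|---|---|---|---|
| 321.75 | 5.46% | 5.43% | 5.58% | 5.6% |
| 270.0 | 5.96% | 5.92% | 6.10% | 6.1% |
| 227.5 | 6.50% | 6.44% | 6.66% | 6.7% |

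Only the continuity-corrected form with a design effect of 1 gives the stated values. Under that form the rounded figures leave room for a common design effect of about 1.00 to 1.01 and no more, so they contain no weighting loss.

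**3. Weighting factor.** With M the number of eligible children in a household that has at least one, Kish's approximation is K = E[M²] / E[M]². The documents do not give the distribution of M, so K is an assumption. Examples:

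- 90% of eligible households with one child and 10% with two: K = 1.07
- Half with one and half with two: 2.5 / 1.5² = 1.11
- 60% / 30% / 10% with one, two or three: K = 1.20
- Zero-truncated Poisson matched to 65% of households having an eligible child: λ = −ln 0.35 = 1.050, K = 1.27 (matched to 60%: 1.25)

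I use 1.1 to 1.4 as the range, with 1.27 in the middle. K equals 1 only if every eligible household has the same number of eligible children.

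**4. Camp half-widths with n replaced by n/K** (same formula, p = 0.5):

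| Component | Stated | K = 1.1 | K = 1.27 | K = 1.4 |
|---|---|---|---|---|
| Survey, both age groups | 5.6% | 5.9% | 6.3% | 6.6% |
| DBS 1y–6y | 6.1% | 6.4% | 6.9% | 7.2% |
| DBS 7y–14y | 6.7% | 7.0% | 7.5% | 7.9% |

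**5. Settlements.** With m children per cluster (expected number / 56 = 7.95, 7.34, 6.67, 5.93), 1 + (m − 1) × 0.10 gives 1.695, 1.634, 1.567 and 1.493, which round to the stated 1.7, 1.6, 1.6 and 1.5. That fits clustering alone. But a weighting factor of 1.10 with an intracluster correlation (ICC) of 0.075 gives 1.67, 1.62, 1.57 and 1.51, and 1.20 with ICC 0.056 gives 1.67, 1.63, 1.58 and 1.53. These round to the same four values, so the figures cannot tell the readings apart.

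**The case against.** Several points can be made for the plan.

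- **The figures are worst case.** At a true proportion of 75% with K = 1.27, the camp survey half-width is 5.5%, inside the stated 5.6%. This is true, but the plan states its precision at 50%, and at 50% the figure does not hold.
- **Offsets exist.** The continuity correction is conservative by about 0.15 points (5.58 against 5.43). A finite population correction would cancel K = 1.27 at a sampling fraction of 1 − 1/1.27, about 21%. But the plan gives no camp totals and claims no such correction, so this cannot be credited.
- **The analysis is already right.** Weighted survey methods will give valid intervals whatever the planning figure says. This stands: the fault lies in the stated precision, not in the analysis.
- **The sample size does not rest on precision.** Logistics set the 625 households and the 56 clusters, and precision is reported as a consequence. This stands too, and no design decision is overturned.

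Two stronger readings are tempting. A reader might infer that the settlement half-widths are also too small. The design effects fit clustering alone, but the protocol does not say what they contain. The column heading carries a note mark whose note is not in the text available here. Multiplying by K without knowing could count the weighting twice.

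A reader might also infer that the DBS 1y–6y numbers are too high, because a household counts if it has a child aged 1y–6y while the draw may fall on an infant under one year. With ages spread evenly over the 6.5 years of the 6m–6y group, the drawn child is aged 1y–6y with probability 6/6.5, and 0.65 × 6/6.5 = 0.600. That is the plan's 60%, and it yields the tabled 270 and 373.5. The wording is loose, but the numbers can stand.

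**Conclusion.** The point holds for the two registered camps. The 5.6%, 6.1% and 6.7% are those of a simple random sample of children, which contradicts the one-child draw and the weighted analysis in the same protocol. At the plan's 50%, and without a finite population correction, they are too small whenever the number of eligible children varies between households.

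The direction follows from the design, using Kish's approximation. The size does not follow from the documents: for an assumed factor of 1.1 to 1.4 the shortfall is about 0.3 to 1.2 percentage points, and 0.7 to 0.8 points at 1.27. For the settlements the documents support only a request for clarification.

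**What to change.** In section 5, I c and Table 1, state an assumed distribution of eligible children per household for each age group, derive the weighting design effect from it, add it as a column and restate the precision. If the sponsor wishes to claim a finite population correction, give the camp totals and show it.

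In section 5, II d and Table 3, say what the design effects of 1.5 to 1.7 contain. Only if they cover clustering alone, multiply them by the same kind of factor. At 1.1 / 1.27 / 1.4 the settlement half-widths would then be about 6.5 / 7.0 / 7.4% and 6.6 / 7.1 / 7.4% (survey, younger and older group), and 6.9 / 7.4 / 7.8% and 7.1 / 7.6 / 8.0% (DBS).

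The cost is restated and somewhat less favourable precision figures. Household numbers, enrolment, the DBS counts and the analysis stay as they are.

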## II. Makeshift and Informal Settlements (Three-Stage Cluster Sampling)

### a. First Stage Sampling – Selection of Clusters

Population estimates and maps with blocks/subdivisions for the makeshift/informal settlements for Rohingya FDMNs will be obtained from the intersectoral coordination group (ISCG). Rohingya persons living among host (Bangladeshi) communities will not be included.

Logistics and available resources determined that the maximum number of clusters of 13 households is 56. Clusters will be defined using zones/blocks and other subdivisions existing in recent maps. Fifty-six (56) clusters will be selected using population proportional to estimated size (PPES) with ENA software.

Reserve clusters may be implemented only if  $\geq 10\%$  of clusters cannot be reached or if  $\geq 20\%$  of the sample size of children is not reached due to higher than expected non-response or refusal.

### b. Second Stage Sampling – Household Selection

One member of the survey team will arrive in each of the clusters one day before teams are scheduled to interview the cluster. Blocks/zones larger than 200 households will be divided into smaller segments. This division can be done based on existing administrative units (neighborhoods, etc.), natural landmarks (river, road, mountains, etc.), or public places (market, schools, churches, mosques, temples, etc.). One segment will be chosen at random, applying PPS.

On arrival, the team member will identify the local community leader (Mahji) for the block and determine if there is an existing list of households for the selected block or segment of block. If a household list is available, the team member will update the list (adding any households that have joined recently and removing households that have left). If a household list is not available, the team member will work with the community leader to create the list.

Once the list is updated/created, the team member will use a random number generator to select 13 households from the list. A community leader will be selected to help escort the survey team to the selected households the following day.

**c. Third stage sampling – Child selection**

During data collection, team members will generate a line list of children in the household aged 6m–6y and 7y–14y, ordered youngest to oldest. The team will select one child randomly (using simple random sampling) from each age group using a random number generator. Children will be assigned a unique study ID. The caregiver of the selected child(ren) will be consented, enrolled, and interviewed (if consent obtained) using the vaccination coverage assessment questionnaire. DBS samples will also be collected on selected children aged 1y–14y.

**d. Sample size for makeshift camps:**

Thirteen (13) households in 56 clusters will result in a total of 728 households visited. To estimate the expected number of children enrolled we made the following assumptions (Table 1):

- 65% of households will have at least one child aged 6m–6y (for DBS calculations, 60% will have a child aged 1y–6y) and 60% of households will have at least one child aged 7y–14y
- Household non-response rate (i.e., no one home) is 5%
- Child non-response rate (e.g., refusal, child absent from home) is 1% for all children for the survey component of the assessment (primary respondent for the questionnaire is the mother or caregiver); for DBS specimen collection, non-

response is estimated at 10% for children 1y–6y and 20% for children aged 7y–14y

- Coverage for 3 pentavalent doses and the proportion of children with protective antibody levels for tetanus is 50%

Given these assumptions, the expected number of children enrolled for the survey is 445 children aged 6m–6y and 411 children aged 7y–14y in the settlements (Table 1). With a design effect of 1.7 (6m–6y) and 1.6 (7y–14y), this results in a 95% Wilson-Score confidence with precision of 6.2% in both age groups. The enrolment for DBS is 374 children aged 1y–6y and 332 children aged 7y–14y in the settlements (Table 1); the design effect is 1.6 and 1.5, respectively, resulting in a precision of 6.5% (1y–6y) and 6.7% (7y–14y).

The expected total number of children enrolled in the makeshift settlements is 856 for the survey; among these children, 706 will be enrolled for DBS specimen collection.

Table 3. Makeshift camp sample sizes:

| Component       | Age group | # Clusters | # Housholds per cluster | Proportion of households with an eligible child | Household Non-response (i.e., no one home) | Child Non-response (i.e., refusal, not home) | # children expected to be enrolled | Design effect** | Precision |
|-----------------|-----------|------------|-------------------------|-------------------------------------------------|--------------------------------------------|----------------------------------------------|------------------------------------|-----------------|-----------|
| Coverage survey | 6m–6y     | 56         | 13                      | 65%                                             | 5%                                         | 1%                                           | 445.0                              | 1.7             | 6.2%      |
| Coverage survey | 7y–14y    | 56         | 13                      | 60%                                             | 5%                                         | 1%                                           | 410.8                              | 1.6             | 6.2%      |
| DBS             | 1y–6y     | 56         | 13                      | 60%                                             | 5%                                         | 10%                                          | 373.5                              | 1.6             | 6.5%      |
| DBS             | 7y–14y    | 56         | 13                      | 60%                                             | 5%                                         | 20%                                          | 332.0                              | 1.5             | 6.7%      |

### **Survey Teams and Supervision**

The survey will be implemented by six teams, each consisting of 1 team leader, 1 interviewer, 1 person to conduct DBS, and 1 advance (for mapping and listing). Additional persons will be trained and kept as reserve team members. Co-investigators and staff from MOHF&W, Unicef, WHO, and CDC will serve as supervisors.

Incentives will be paid to a community member on each survey day for support in identification of households, mapping of zone boundaries, and support in carrying of equipment.

## **Survey Team Training**

All team members, supervisors, and reserve staff will participate in the training. The survey team will receive a 5 days training (1–5 April 2018) which includes classroom training, standardization test, and field test. In the training, the field enumerators will be trained on survey objectives, household selection techniques, demonstration of dried blood spot technique, content of the questionnaire, and use of mobile data collection. The training will include both lecture and practical sessions.

A field test will be conducted a day before the actual survey in extension areas of Kutupalong Makeshift Settlement. The questionnaire will be translated into Bengali and administered in the local Rohingya language (as there is no written script for the Rohingya language).

## **Data Collection, Management and Analysis Plan**

Data collection will take place in Kutupalong refugee camp over the course of about 1 week, in makeshift and informal settlements over the course of 3–4 weeks, and Nayapara refugee camp over the course of about 1 week.

Data will be collected on tablets (Lenovo). Data will be uploaded daily to a Kobo server to enable remote monitoring of data quality. All teams will carry hard copies of the questionnaires as back-ups in case the tablet fails at any point.

A daily random check of entered data will be conducted by the survey manager. Team leaders with respective program personnel will ensure quality data collection at field level.

Vaccination coverage, seroprevalence and respective 95% confidence intervals will be estimated for 6m–6yr old children and 7–14yr old children using survey methods that account for the cluster design and sampling weights.

## **Dried Blood Spots (DBS)/Serologic Assessment**

### **I. Collection of dried blood spot (DBS) specimens**

The team will assign the HH and the children the appropriate ID numbers. The lab technician collecting DBS will ensure that children selected for DBS has been appropriately consented, enrolled, and a unique identifier (ID) assigned (described elsewhere).

The lab technician and assistant will place a clean mat on a table or rug, and organize the required supplies on the mat, including a lancet, alcohol swabs, sterile gauze, band-aid, DBS card with two specimen labels pre-attached, labels for the unique ID, and marker. The lab technician will attach on the DBS card two labels with the child's unique ID number. The

unique ID should be recorded alongside the child's questionnaire in the data collection tablet.

The technician will clean his/her hands with sanitizer, and don new gloves. After cleaning a fingertip from the child's second or third finger with an alcohol swab, the technician will do a finger prick using a single-use blood lancet. Holding the finger downside above one circle on the DBS card and applying gentle pressure without squeezing, the technician will ensure that one drop of free-flowing blood falls onto and saturates one of the 15 millimetre circles on the DBS card. The process will be repeated to complete at least three of the five circles (one drop per circle).

Once the dried blood spots have been filled, the technician or assistant, without touching the blood spots, will place the DBS card in a portable drying rack inside a plastic container to allow drying. Once this is completed, the technician will apply a sterile gauze to the prick site until bleeding stops.

If there is another eligible child in the household, the technician will conduct another prick as explained above and store the DBS card in the drying rack as before.

